## 7. Participation Attendance/Adherence

Individual participation in each PE session will be scored with 0 (zero) if the participant does not attend or 1 (one) if the participant is present at the PE session and participates in it. At the end of the interventions, the participants who do not perform at least 75% of the sessions will be excluded from data processing.

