## Abstract

We developed a physical exercise (PE) program for people with Intellectual and Developmental Disabilities (IDD), aiming to determine the effects on physical fitness, health, cognitive ability, and quality of life (QoL). Using experimental methodology, this intervention study recruited 21 adults (18 to 65 years old), institutionalized and with no other associated pathology, who will be allocated to one of the different groups: (i) gym/indoor intervention group (using weight machines), (ii) outdoor intervention group (using low-cost materials), or (iii) control group (without specific intervention, who continue with their normal daily activities). Both intervention groups will engage in 45 min of training per session, twice a week, for 24 weeks. Assessments will be conducted at baseline (initial assessment), 3 months (mid-term assessment), and 6 months (final assessment). Variables assessed include anthropometrics, body composition, functional capacity, muscle strength, general health, cognitive ability, and QoL. The results of this study will assist in the development of more effective strategies, recommendations, and interventions to ensure better and greater adherence to PE by institutionalized individuals with IDD, namely, recommendations for assessment, prescription, and implementation of PE for this population. Additionally, we intend to make available two PE programs, if they are adapted and promote positive effects.

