Despite the importance of PA and/or PE benefits, this population has high rates of sedentarism and low levels of physical activity engagement [16,17], not meeting the recommendations [18,19], which puts them at greater risk of developing chronic diseases [20] and consequent premature death [21,22]. The risks of physical inactivity in people with disabilities increase when compared to the general population: higher prevalence of hypertension (25 to 41% compared to 29% in the general population); obesity (30.8 to 36.6% compared to 18.2 to 18.5%); and metabolic syndrome (21 to 29.3% compared to 13.5% to 17.9%) [23,24]. In addition, as the degree of disability increases, physical activity levels decrease more significantly [25], affecting their physical fitness, capacity to perform activities of daily living, and independence [26]. To promote their life conditions, people with IDD should be integrated into PA and PE practice, according to recent recommendations [18,19].

One of the possible reasons for these low levels of practice is the existence of barriers that hinder their practice. Among them, we can find factors such as financial cost and lack of adapted PE [27,28]. To reduce the impact of these barriers, it is important to develop PEs. Besides being adapted to the individuals, they must be accessible to any type of context and financial availability, both for the individuals and the support institutions. In addition, the development of these PE may contribute to the reduction in the risk of the onset of metabolic and cardiovascular diseases, which decreases healthcare costs and promotes physical fitness, functionality, and QoL. Therefore, the main objective of the present study is to evaluate and compare the effectiveness of two different 24-week PE programs on levels of physical fitness, general health, dementia/cognitive decline, and QoL in individuals with IDD.

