## 2. Materials and Methods

### 2.1. Study Design

The present study protocol describes a non-randomized experimental study, consisting of three groups (1:1 allocation), to assess and compare the effectiveness of two different combined PE (strength + aerobic capacity) for individuals with IDD.

Participants will be allocated to one of the three groups: (i) indoor training group (IG) with sessions carried out in a gym, using weight machines; (ii) outdoor training group (OG) with sessions using low-cost materials; and (iii) control group (CG) with participants continuing to do their normal activities (participation in one of the exercise interventions will not be allowed), based on their interests and availability to be involved with PE programs.

Participants from both intervention groups will participate twice a week, in a 24-week supervised PE program, with sessions lasting 45 min per session. All outcome measures will be collected at three different time moments, at baseline (time 0, baseline assessment, or week 0), at mid-term (time 1, intermidiate assessment, week 12), and at the end of the intervention program time 2, final assessment, week 24). The measurements will be performed after 48 h, after the last workout in both groups, and always in the morning. Figure 1 shows the participant flow for this trial.

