#### 2.4.3. Control Group

Subjects in the control group will be encouraged to keep their usual lifestyle and their attendance at exercise sessions corresponding to the two exercise programs will not be allowed.

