## 5. Procedures

Intervention study that involves several phases: (a) design of PE programs; (b) promotion of the program (information pamphlets will be distributed to the target people with IDD/guardians/tutors/caregivers about the study procedures and aims); (c) sample recruitment (participants/parents/tutors will sign an informed consent form and all project will be carried out in accordance with the Declaration of Helsinki; (d) division according to their intention to participate in the study: (i) IG/indoor context (using weight machines), (ii) OG (low cost), or (iii) CG (no specific intervention; continue with normal daily activities); (e) initial evaluation of the groups by an evaluator blinded to the group belonging; (f) intermidiate evaluation of the groups by an evaluator blinded to the group belonging; (g) final evaluation of the groups by an evaluator blinded to the group belonging; (h) data analysis: descriptive, comparison between groups and conditions, comparison before and after, correlations, among others (subjects who do not perform at least 75% of the sessions will be excluded from data processing).

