## 6. Adverse Events

Despite all safety procedures adopted/provided, participants may, at some moment, experience some adverse effects, as well as be aware of some unlikely risks, during the assessment protocols or even during the interventions. When starting a PE program, people who, as a rule, adopt a sedentary lifestyle, run the risk of experiencing some type of discomfort, fatigue, or muscle pain. Given that the intensity will be gradually increased, it is expected that muscle pain will be light and brief, mitigating with the muscle’s habit of exertion. Therefore, the leader will be available for any dialogue throughout the project, to help and advise the participants.

Likewise, participants who develop any type of physical injury or other health problem during the interventions will be referred to the institutional physiotherapy office or family doctor and their continuation in the project will depend on the consideration of all related parties. All adverse physical and psychological outcomes will be recorded, described, and reported in future publications.

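### The 75% attendance rule removes people from the exercise groups only, by post-allocation behaviour, and can bias the group comparisons by an amount and in a direction that the protocol does not let us fix

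*Protocol article*

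**What the plan says.** Section 7 (Participation Attendance/Adherence) defines the score and the rule. "Individual participation in each PE session will be scored with 0 (zero) if the participant does not attend", and 1 if present and taking part. At the end of the interventions "the participants who do not perform at least 75% of the sessions will be excluded from data processing".

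Section 5 (Procedures), item (h), repeats it in the line that lists the descriptive, between-group, before-after and correlation analyses: "subjects who do not perform at least 75% of the sessions will be excluded from data processing".

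The sessions belong to the two exercise programmes. In Section 2.1, "Participants from both intervention groups will participate twice a week, in a 24-week supervised PE program". For controls, Section 2.4.3 says that "their attendance at exercise sessions corresponding to the two exercise programs will not be allowed".

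The main objective in Section 1 is to "evaluate and compare the effectiveness of two different 24-week PE programs", and the hypotheses there concern change after 12 and/or 24 weeks. The article names no analysis of all participants and does not call the 75% set per-protocol or secondary.

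**The concern.** Attendance is observed after people have entered a group, and it can depend on how they fare in it. Section 6 describes one route: after an injury or other health problem, "their continuation in the project will depend on the consideration of all related parties". Dislike or poor tolerance of a programme are others. If such people also gain less, removing them makes the remaining group look better than the programme performed.

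Two features make this worse than an ordinary completers' analysis. The control group loses nobody, so the selection does not balance out in exercise versus control. And if one programme is harder to attend than the other, the indoor-outdoor comparison sets a more selected group against a less selected one. The trial would then report results in good attenders as the effectiveness of the programmes, from groups of about seven.

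**Working it through.** **1. The threshold.** Sessions: 2 × 24 = 48 (Section 2.1). Cut-off: 0.75 × 48 = 36. A participant with 36 sessions stays (75%). One with 35 goes (35/48 = 72.9%). Missing 13 or more therefore means exclusion.

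**2. Who can be excluded.** The score exists only for exercise sessions, and controls may not attend them. Read literally, every control would have 0% and be removed, leaving no comparison. Read sensibly, the rule does not apply to controls and acts only on the indoor and outdoor groups.

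**3. Week-12 data.** Someone who attends all 24 sessions up to week 12, is assessed, and then stops has 24/48 = 50%. The rule is applied at the end and removes the person entirely, including a baseline-to-week-12 change after full attendance. The hypotheses in Section 1 name that time point.

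**4. Group size.** 21 participants in three groups at 1:1 (Sections 2.1 and 2.2) give 21/3 = 7. One exclusion is 1/7 = 14% of a group.

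**5. Possible size of the shift.** Two inputs are missing from the documents and are assumed here: the number excluded (1 or 2 of 7) and the correlation *r* between attendance and change (0.3 to 0.5, with 0 and −0.3 for contrast). Attendance and change are taken as jointly normal, and any programme effect as the same for everyone.

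In a large group, removing the lowest fraction *q* of attenders shifts the mean change of those kept by *r* × φ(z_q)/(1 − q), in SDs of change. For seven people the formula runs high, so the shift was also simulated with n = 7 (200,000 groups per setting):

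| Removed | r | Large-sample formula | Simulation, n = 7 |
|---|---|---|---|
| 1 of 7 | 0.3 | +0.079 | +0.070 |
| 1 of 7 | 0.5 | +0.132 | +0.113 |
| 2 of 7 | 0.3 | +0.143 | +0.127 |
| 2 of 7 | 0.5 | +0.238 | +0.212 |
| 1 or 2 of 7 | 0 | 0 | not run |
| 1 of 7 | −0.3 | −0.079 | not run |
| 2 of 7 | −0.3 | −0.143 | not run |

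The control mean does not move in any row, so the shift passes in full into exercise versus control. For indoor versus outdoor, equal losses at equal *r* cancel. With 2 lost from one group and 1 from the other, the net shift is 0.127 − 0.070 = 0.057 SD (r = 0.3) to 0.212 − 0.113 = 0.099 SD (r = 0.5). With 2 against none it is 0.127 to 0.212 SD.

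**6. The plan's sample size.** Section 2.2 requires at least 15. Reading the effect size 0.5 as Cohen's f, with three groups, three measurements, an assumed correlation of 0.5 and sphericity, the within-subject test needs 13, or 15 in equal groups (power 0.984). So 15 can be reproduced. It says nothing about who may be left out.

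**The case against.** **Direction.** A reader might infer that the rule must inflate both programmes. The documents do not support that. They give no relation between attendance and outcome, and the least fit may attend least yet have most room to improve. This stands: upward is plausible, not established.

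**Frequency.** Exclusions may be few. Section 2.2 excludes people who cannot commit for six months, and Section 2.4 provides supervised sessions with intensity adjusted so that people can take part. This also stands, and it is why the number excluded is treated as unknown. It does not justify the rule, because if few are excluded little is lost by keeping them.

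**Sample-size margin.** Recruiting 21 against a required 15 leaves 6 spare. A margin protects precision; it does not correct a one-sided selection.

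**Small-sample testing.** A reader might infer that two exclusions, leaving n = 5, make significance impossible. That holds only for an exact two-sided signed-rank test (minimum p = 2/32 = 0.0625), which Section 8 does not specify. The normal approximation reaches z = 2.02, p = 0.043. Friedman's test over three times can reach 6/6⁵ = 0.0008, and the Kruskal–Wallis comparison is not subject to this limit.

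**Harms.** A reader might infer that injured participants disappear from safety reporting. Section 6 already promises that all adverse outcomes will be recorded and reported. Only the relation of the exclusion to that promise needs stating.

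**Adherence as an aim.** The Abstract hopes that the results will help "to ensure better and greater adherence to PE by institutionalized individuals with IDD". That is a later use of the results. No objective or hypothesis concerns adherence, so the case rests on the effectiveness objective.

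**No randomisation.** Groups form by interest and availability, which the article admits as a limitation, so an all-participants analysis is confounded too. True, but the attendance rule adds a second, avoidable selection that is not among the listed limitations.

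**Conclusion.** The point holds. Two sections fix an analysis set that depends on post-allocation behaviour, can sensibly remove people from the exercise groups only, and drops usable week-12 data. This is a stated rule, not a detail left to an analysis plan that is not shown. That part follows from the text alone.

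The resulting bias is possible and probably upward if low attenders improve less, but its sign and size are unknown. About 0.07 to 0.11 SD for one exclusion of seven, and 0.13 to 0.21 SD for two, rest on the assumed correlations of 0.3 to 0.5 and assumed counts. They are illustrations, not estimates for this trial. The rule should be changed before the data are analysed, because a choice of analysis set made after seeing attendance and outcomes would not be credible.

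**What to change.** In Sections 5 and 7, replace the exclusion with the following:

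- **Main analysis:** every participant with a follow-up measurement, in the group entered, whatever the attendance. Someone measured at week 12 but not at week 24 enters the week-12 comparisons.
- **Sensitivity analysis:** the set with at least 36 of 48 sessions, labelled per-protocol, with a statement of how controls are handled in it.
- **Reporting:** attendance by programme, and the number below the threshold with reasons, by group.
- **Safety:** a sentence saying that the attendance threshold does not apply to the adverse-event reporting promised in Section 6.
- **Follow-up:** where feasible, invite people who stop to the week-12 and week-24 assessments, which are already scheduled.

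Most of this is wording, and attendance is already recorded at each session. The real costs are the effort of bringing people who have stopped to the university laboratory, and a main effect that may look smaller than in good attenders. The change does not remove the confounding from non-random allocation; it removes only the selection that this rule adds.

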## 8. Statistical Analysis

In the statistical analysis, descriptive parameters will be used (mean ± standard deviation or percentage) normality and homogeneity will be verified through the *Shapiro*–*Wilk* test and the *Levene* tests, respectively. The existence of significant differences between groups will be analyzed using the *Kruskal*–*Wallis* test and between times using *Wilcoxon* or *Friedman* test. The non-parametric statistic was defined according to the “Central Limit Theorem” [63], in the sense that it will require 30 participants in the sample to have a normal distribution. The magnitudes of the differences will be examined using the *Cohen’s d* effect size [64]. Likewise, associations across studies variables will be verified through the *Spearman* coefficient of bivariate correlations (*r* = 0.10 to 0.29—small; *r* = 0.30 to 0.49—moderate; *r* = 0.50 to 1—strong) [65]. The significance level adopted for all analyses will be *p* < 0.05. For data processing, the computer program *Statistical Package for Social Sciences* (SPSS Science, Chicago, IL, USA), version 28 will be used.

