Therefore, the following hypotheses will be operationalized: (i) individual with IDD increased physical fitness after 12 and/or 24 weeks of PE; (ii) individual with IDD increased general health after 12 and/or 24 weeks of PE; (iii) individual with IDD increased dementia/cognitive decline after 12 and/or 24 weeks of PE; (iv) individual with IDD increased QoL decline after 12 and/or 24 weeks of PE; (v) there was a difference between groups on levels of physical fitness after 12 and/or 24 weeks of PE; (vi) there was a difference between groups on levels of general health after 12 and/or 24 weeks of PE; (vii) there was a difference between groups on levels of dementia/cognitive decline after 12 and/or 24 weeks of PE; and (viii) there was a difference between groups on levels of QoL after 12 and/or 24 weeks of PE.

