### 2.2. Participants

Adult volunteers, institutionalized in a support institution, located in Leiria, Portugal, recruited by the non-probabilistic convenience method will participate in the program.

In the first step, an individual explanation will be held about the procedures and objectives of the study, as well as the potential benefits, risks, and the time needed for the development of the project.

In a second moment, the participants/family members/tutors will sign a free consent form. Inclusion criteria will be defined: (1) adults with IDD, diagnosed with mild, moderate, or severe IDD; (2) age over 18 years) success in performing movements such as pulling/pushing; (3) capacity to perform the assessments. Exclusion criteria will be defined: (1) individuals who cannot commit themselves for 6 months; (2) individuals with other associated pathologies; (3) contraindications to PE (e.g., high blood pressure); (4) inability to walk unaided; (5) profound IDD; (6) inability to communicate; (7) non-delivery of signed informed consent.

Due to the characteristics of this special population and logistical constraints intrinsic to the development of intervention studies, the sample will consist of the first 21 individuals who agree to participate in the program, aged between 18 and 65. After that, participants will be allocated to one of the three groups. A power analysis (calculated using *G*Power*, version 3.1.9.7 [29] showed that a sample of at least 15 was required to detect a medium effect size (*ES*) of 0.5 (*α* = 0.05, 1 − *β* = 0.95) using a repeated-measures analysis of variance (*ANOVA*), in agreement with some previous studies [30,31]. The effect size of 0.5 was chosen given that this value was verified from studies investigated the effects of exercise on the variables of interest in our study [32,33,34].

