## 9. Discussion

This study will allow us to investigate and compare the effectiveness of two different 24-week exercise programs, in different environments, on the levels of the physical fitness, general health, cognitive ability, and quality of life of individuals with IDD. We intend to evaluate a set of quantitative variables at the same time, with the expectation that participants in the intervention groups will show positive changes, taking into consideration previous studies [4,32]. In the control group, no changes in the variables analyzed are expected. It is believed that the expected results can be attributed to the physical and physiological effects of the environment associated with the different exercise protocols proposed, as there is evidence that finds disparate results in PE programs performed in different contexts [66]. The results will be published at the conclusion of the study.

The pilot study that will follow is essential to understand if these two PE programs are effective tools to reduce barriers that hinder/impede their practice [27,28], and their effectiveness in promoting the variables assessed, taking into account the low levels of physical fitness and QoL of this population. Likewise, we intend to contribute with implications for the practice with new interventions with physical exercise, prescription, and effective strategies, which we believe can contribute, at all levels, to individuals with IDD.

The expected physiological benefits are based on the hypothesis that regular PE practice leads to adaptations in both the cardiovascular and musculoskeletal systems that support an overall increase in exercise capacity and performance [66]. It is considered an ideal tool in the prevention and treatment of various types of cardiometabolic diseases, a promoter of physical fitness, performance activities of daily living, and in reducing/mitigating sarcopenia and cognition decline. In addition, neuromuscular mechanisms, namely, the increased expression of neurotrophic factors (i.e., BDNF), the increase in serotonin and norepinephrine, the regulation of the HPA axis activity, and decreased systemic inflammatory signaling [67,68,69,70,71], may be associated with cognitive decline and QoL.

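### The indoor-versus-outdoor comparison in the main objective has no test of its own: the only between-group test named is a three-group Kruskal-Wallis

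*Protocol article*

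**What the plan says.** The Introduction states that "the main objective of the present study is to evaluate and compare the effectiveness of two different 24-week PE programs". Section 2.1 repeats the aim and sets the design: "a non-randomized experimental study, consisting of three groups (1:1 allocation), to assess and compare the effectiveness of two different combined PE". The third group is a control that takes part in neither programme.

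The between-group hypotheses (v)-(viii) share one pattern, for example "there was a difference between groups on levels of physical fitness after 12 and/or 24 weeks of PE". None says which groups are meant.

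Section 8 gives the tests: "The existence of significant differences between groups will be analyzed using the *Kruskal*–*Wallis* test and between times using *Wilcoxon* or *Friedman* test". Wilcoxon is thus assigned to comparisons over time, not between groups. Two further sentences bear on the point: "The magnitudes of the differences will be examined using the *Cohen’s d* effect size" and "The significance level adopted for all analyses will be *p* < 0.05". Section 5 refers to group comparisons in general terms only. No indoor-versus-outdoor, indoor-versus-control or outdoor-versus-control contrast is named anywhere in the article.

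The Discussion (section 9) expects gains in the intervention groups and no change in control. It links the expected results to the training environment, noting that "there is evidence that finds disparate results in PE programs performed in different contexts".

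**The concern.** The comparative part of the objective has the null hypothesis indoor = outdoor. The named test has the null hypothesis indoor = outdoor = control. These differ most in the situation the Discussion anticipates, with both programmes improving and control unchanged. The omnibus null is then false whether or not the programmes differ, so its rejection carries no specific information about indoor versus outdoor.

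Because hypotheses (v)-(viii) ask only for some difference between groups, that rejection would confirm them. At stake is the interpretation of the main comparison: a plain exercise-versus-control effect would satisfy every between-group hypothesis, while the question of gym against low-cost outdoor training would have been neither tested nor answered.

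**Working it through.** **The plan's own figure.** The article gives no figure for indoor versus outdoor. Its only power statement (section 2.2) is a minimum of 15 for an effect size of 0.5, alpha 0.05 and power 0.95 with repeated-measures ANOVA. Taking f = 0.5, k = 3 groups and m = 3 measurements, and assuming correlation 0.5 and sphericity:

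- Time effect: λ = f²·N·m/(1−ρ) = 0.25 × 15 × 3/0.5 = 22.5 on (2, 24) df, power 0.984. The smallest N in equal groups is 15, which matches.
- Group effect: λ = f²·N·m/(1+(m−1)ρ) = 0.25 × 15 × 3/2 = 5.625 on (2, 12) df, power 0.449. The required N is 45.

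The article does not say which effect was powered, and other settings can also return 15. One is the interaction with two measurements and correlation 0.7. Nothing shows that the figure was aimed at the two-programme contrast.

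**Inputs for the check**

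- Total of 21: "the sample will consist of the first 21 individuals who agree to participate in the program" (section 2.2). With three equal groups, n = 21/3 = 7.
- Alpha 0.05 (section 8).
- Assumed, because the article gives no outcome SDs: normal data, SD 1, and the sizes of the shifts from control.
- Assumed as a sensitivity case: 5 per group, since section 7 excludes participants below 75% attendance and the number lost is unknown.

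**Step 1: one data set by hand.** Let control hold ranks 1-7 (sum 28), and let the two programmes share ranks 8-21 as evenly as possible (sums 101 and 102).

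H = 12/[N(N+1)] × Σ(R²/n) − 3(N+1)

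= 12/(21 × 22) × (28² + 101² + 102²)/7 − 66

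= 0.025974 × 3055.571 − 66 = 13.37

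On 2 df, p = exp(−13.37/2) = 0.001. For indoor versus outdoor alone, the rank sums within the 14 are 101 − 49 = 52 and 102 − 49 = 53. So U = 52 − 28 = 24 against an expected 24.5, and exact p = 1.0. The planned test is highly significant on data showing no difference between the programmes.

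**Step 2: how often.** Simulation, 20,000 trials per setting, programmes identical, both shifted from control. Kruskal-Wallis uses the chi-square reference; Mann-Whitney is exact.

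| Shift of both programmes from control (SD) | Kruskal-Wallis significant, n = 7 | Mann-Whitney indoor vs outdoor, n = 7 | Kruskal-Wallis significant, n = 5 |
|---|---|---|---|
| 0 | 4% | 4% | 4% |
| 0.5 | 12% | 4% | 9% |
| 0.8 | 25% | 4% | 17% |
| 1.0 | 37% | 4% | 25% |
| 1.5 | 71% | 4% | 52% |
| 2.0 | 93% | 4% | 77% |

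The first row shows that the omnibus test holds its level when all three groups are equal. The later rows are its power to detect that control differs.

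**Step 3: what a direct test could achieve.** At 7 versus 7, an exact Mann-Whitney test of indoor versus outdoor has power of about 11% at 0.5 SD and 34% at 1 SD. A t-test needs a difference of about 1.63 SD for 80% power. Requiring a significant Kruskal-Wallis first lowers the 34% to about 25% when control lies midway between the programmes, and to about 28% when one programme equals control.

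**The case against.** Four points can be made for the plan.

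- **Follow-up tests are often left to an analysis plan.** None is shown, and section 8 does not rule them out. If the point were only that a post hoc procedure is unspecified, this would dispose of it. What stands against it is that section 8 does say which test settles between-group differences, and that test does not match the comparative objective. The loosely worded hypotheses are also protocol text.
- **The objective is wider than one contrast.** It covers evaluating each programme as well as comparing them, which is why there is a control group, and the omnibus test does fit hypotheses (v)-(viii) as worded. This is correct. The gap concerns the comparison of the two programmes, not the whole objective.
- **Cohen's d is a two-group measure** and could describe indoor versus outdoor. It could, but section 8 attaches it to no pair, and it supplies an effect size without a test.
- **The rejection rates are not errors.** When both programmes beat control, the omnibus null is false and rejecting it is right. A reader might infer that the 12% to 93% rates are inflated alpha, or that the protocol directs a significant Kruskal-Wallis result to be reported as a gym-versus-outdoor difference. The document supports neither reading. The first confuses power with type I error. On the second, the Discussion's remark on environment is an expected explanation and not a rule for interpreting a p-value.

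**Conclusion.** The point holds in limited form. Followed as written, section 8 provides no test of indoor against outdoor, and hypotheses (v)-(viii) can be met by an exercise-versus-control effect alone. With identical programmes this would happen in about 37% of trials at a 1 SD advantage over control and 93% at 2 SD (25% and 77% with 5 per group). It becomes a wrong conclusion only if it is reported as a difference between programmes. A reader might go further and say that the plan cannot address its main objective at all. That is too strong, because evaluation against control and a descriptive pairwise effect size remain possible.

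The percentages rest on assumed normal data, equal groups and chosen shifts. The mismatch between test and comparison does not depend on them. The point should be corrected before analysis.

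**What to change.** In section 8:

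1. Analyse change from baseline, because participants choose their group and may differ at the start. Use the same change scores for the gate and the pairwise tests.
2. Keep Kruskal-Wallis at 0.05 as the gate. If it is significant, run exact Mann-Whitney tests at 0.05 for indoor vs outdoor, indoor vs control and outdoor vs control. With three groups this is a closed procedure: any two true pairwise equalities imply the third. So either all three are true and the gate limits the error to 5%, or at most one is true and its own test does.
3. State that the programme comparison is read only from indoor vs outdoor.
4. Report each contrast as a Hodges-Lehmann difference with 95% CI, whatever the gate shows.

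In the Introduction, reword hypotheses (v)-(viii) to name the pair compared.

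**Cost.** Some wording and a few more lines of output. The 5% control applies to each outcome at each analysed time point, not across the many outcomes. Gating costs some power (about 25% instead of 34% at a 1 SD programme difference with control midway). Change scores reduce the effect of baseline differences but do not remove the bias of self-selected groups. The contrast stays imprecise at 7 versus 7, so the plan should state that a non-significant indoor-outdoor result is not evidence of equivalence.
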